### Follow up and data collection

Data extraction will be undertaken as a single data extract at least one year after targeted case-finding has been implemented in the last practice. This allows for at least a year of follow up. The number of untreated high-risk patients who are started on treatment will be assessed at the start of each step in the stepped wedge trial. An outline of the data extracted is given in Table
1.

**Table 1 T1:** Data to be extracted from electronic primary care records at the end of the study

**Data to be extracted**	
Patient characteristics	Age
	Sex
	Ethnicity
	Date of death,
	Date of leaving practice
Diagnoses and dates of diagnoses	Diabetic status
	Smoking status
	Angina
	MI
	TIA
	Stroke
	Peripheral vascular disease
	Death
Cardiovascular risk factor status and dates	Smoking status
	Systolic blood pressures
	Diastolic blood pressures
	Total cholesterol
	HDL cholesterol
	Family history of premature coronary heart disease
	Left ventricular hypertrophy
Prescriptions and dates of prescriptions	BNF Chapter 2.2.1 Thiazide and related diuretics
	BNF Chapter 2.2.3 Potassium-sparing diuretics and other diuretics
	BNF Chapter 2.2.4 Potassium-sparing diuretics with other diuretics
	BNF Chapter 2.4 Beta-blockers
	BNF Chapter 2.5.1 Vasodilator antihypertensives
	BNF Chapter 2.5.3 Adrenergic neurone blocking drugs
	BNF Chapter 2.5.4 Alpha blockers
	BNF Chapter 2.5.2 Centrally acting antihypertensives
	BNF Chapter 2.5.5.1 ACE inhibitors
	BNF Chapter 2.5.5.2 ARB-2
	BNF Chapter 2.6.2 Calcium-channel blockers
	BNF Chapter 2.8.1 Parenenteral anticoagulant
	BNF Chapter 2.8.2 Oral anticoagulant
	BNF Chapter 2.9 Antiplatelet drug
	BNF Chapter 2.12 Lipid lowering drug
	Over the counter aspirin use

### Analysis

The characteristics of the populations served by the GP practice will be summarised, including, primary care trust, list size, age of practice population, gender, ethnicity and practice Index of Multiple Deprivation score.
[30] These characteristics will be summarised by numbers and percentages, means and standard deviations or medians and inter-quartile ranges as appropriate. We will then report the number of patients excluded in the study by each of the inclusion criteria (age, CVD status and medication use), and also the number of patients meeting the study inclusion criteria.

Fidelity of uptake will be explored by reporting, the number of patients invited, the number of patients seen by the nurse/prescribing advisor and the proportion who were subsequently confirmed to have a CVD risk ≥20%.

The characteristics of the patients included in the invited population will also be summarised. These characteristics will include gender, age, blood pressure, lipids, glucose, medication use (at baseline), cardio-vascular disease, smoking status, Framingham risk score, and referrals to smoking cessation, physical advice and dietetic advice services. These characteristics will be summarised by their values at baseline (2008) and will be compared between those not attending; and for those attending stratified by whether their calculated risk was greater than 20%.

The primary aim of the study is to evaluate whether there is a difference in proportion of eligible patients on the relevant prescription medication before and after the practice was exposed to the intervention. In statistical terms this null-hypothesis (no difference) can be tested using a mixed logistic regression model with binary outcome (prescription of the appropriate medication). Important independent variables to consider are the clustering effect (i.e. effect of GP practice), calendar time effect (since the intervention is sequentially rolled-out) and an indicator of intervention exposure for each practice at each time point; in an to adjustment for other characteristics [4]. These models will be fitted using population averaged models using GEE methods in STATA, allowing for clustering and adjusting for individual level covariates and any cluster level covariates where available. Population averaged models as opposed to random effects models (also known as marginal models) will be used as within the framework of cluster randomised trials, random effects models both lack appropriate interpretation and might be biased
[31]. The covariates to be included in the adjustment will be pre-specified and will include practice size and patient level characteristics (age, sex, diabetic status, smoking status, blood pressure, total cholesterol and HDL cholesterol); GP practice will be included as a random effect; time point as a fixed effect; and exposure or non-exposure as the main intervention effect. Null hypotheses for secondary outcomes take a similar form to that for the primary outcome. Analysis of the secondary outcomes will take a similar form to that described for the primary outcome.

The primary outcome will be considered significant at the 5% level and so 95% confidence intervals (CIs) reported; whereas secondary outcomes will be deemed significant at the 1% level (and so 99% CIs reported). This difference in levels of significance, give more weight to the primary outcomes. Analysis will be stratified by primary care trust: the analysis of the project nurse led intervention in Sandwell and the prescribing advisor led intervention in Solihull will be carried out separately.

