### Sample size & number of practices

Since the analysis is to be stratified by primary care trust sample size calculations were also stratified by trust. However, since this is a pragmatic evaluation the study has a limited sample size to those practices which agreed to participate in the evaluation. In the Solihull trust only 6 practices agreed to participate and it was not expected that this would provide adequate power. We therefore based power calculations on the Sandwell part of the study only. In the pilot study approximately 5% to 6% of registered patients in each practice were found to be untreated high risk patients. In Sandwell this means we expect to invite between 6,241 and 7,489 untreated high-risk patients from a total registered population of 124,820. From this fixed study size, it is possible to estimate the difference that will be detectable (difference between patients exposed and not exposed to the intervention in proportion of eligible patients medicated). These patients are spread across 26 clusters, each with a conservative estimate of average size of 240 (assuming 5% of patients eligible); but with some variation between practices sizes with coefficient of variation of 0.74.

The difference detectable depends on the level of intra-cluster correlation (ICC), the variation in sizes of practices, and the proportion of patients medicated in the control arm. Estimates of ICC would ideally come from other similar studies, but in the absence of such evidence we are guided by a review of estimates of ICCs which found that ICC values are typically between 0.02 and 0.1
[32]. The stepped wedge nature of this study should mean that impact of intra-cluster correlations are lower than in conventional cluster trials
[4], so these values can be viewed as conservative. The pilot study estimated that the proportion of eligible patients started on medication over the course of one year is around 13%.

So, using several different estimates of likely values of ICCs and current proportions of patients medicated, we have estimated what values for outcomes post intervention could be detected (all for 80% power, 5% significance and coefficient of variation of 0.74). We have used conventional cluster RCT power calculation methods since this study is a modification of the conventional stepped wedge design and so provide conservative estimates
[33].

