## Discussion

There is very limited published evidence for the benefit of targeted case finding for CVD over opportunistic case finding. The prevention and early treatment of CVD, as the biggest killer and a major cause of morbidity in the UK, has the potential to make huge impacts to the health of populations. We have presented the design and methods for a stepped wedged cluster RCT to assess the benefits of systematic case finding of patients at high risk of CVD over opportunistic assessments.

There were strong imperatives to implement the cardiovascular prevention project across all practices due to a widespread consensus that this type of case finding approach “made sense” and the benefits of early intervention in CVD and diabetes are well known. In addition the practices served deprived populations where the burden of cardiovascular disease was relatively high compared to the rest of the country and clinicians felt a responsibility to give their patients these opportunities to improve their health. The mandate to implement case finding in all practices meant it was not possible to conduct a cluster randomised controlled trial, however the stepped wedged cluster design allows the process of implementation to be structured in such a way as to ensure that an evaluation of targeted versus opportunistic case finding could be undertaken.

The limitations that are present in this study, were largely as a result of the need to work with the enthusiasm that existed to implement this approach and evaluate a real world roll out of this approach in the most robust way possible. The study was implemented at a time when the NHS were rolling out health checks in those aged 40 to 74. This might induce contamination, whereby those practices included in this study might also have rolled out the NHS health checks. The study also was limited in its size to those primary care practices which agreed to participate.

One further limitation of this study is the relatively small number of clusters included. The MRC guidelines suggest that a minimum of 10 clusters should be used in each arm of a cluster randomized trial

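### The primary model is specified both as a population-averaged GEE and with a practice random effect; one must be named, and if it is GEE, the inference must suit 26 practices

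*Protocol article*

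**What the plan says.** All of the model text stands in one paragraph of the Analysis section of the protocol article. In order, it says:

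- The primary null hypothesis "can be tested using a mixed logistic regression model with binary outcome".
- "These models will be fitted using population averaged models using GEE methods in STATA", with allowance for clustering and covariate adjustment.
- The reason for this choice is that in cluster randomised trials "random effects models both lack appropriate interpretation and might be biased".
- In the list of model terms, "GP practice will be included as a random effect; time point as a fixed effect", with exposure as the intervention effect.

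The next paragraph sets the error level: "The primary outcome will be considered significant at the 5% level and so 95% confidence intervals (CIs) reported". It adds "Analysis will be stratified by primary care trust", with Sandwell and Solihull analysed separately. For Sandwell, the Sample size section says "These patients are spread across 26 clusters" and gives an average of 240 eligible patients per practice and a coefficient of variation (CV) of practice size of 0.74.

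The Discussion concedes "One further limitation of this study is the relatively small number of clusters included". It then argues that the stepped wedge may lessen the problem, because each practice is its own control and the intra-cluster correlation matters less.

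The article does not give the working correlation, the type of standard error, the reference distribution or the number of steps.

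**The concern.** A marginal logistic model fitted by GEE and a logistic model with a practice random effect differ in what they estimate. The first compares the proportion started on treatment averaged over practices. The second compares the odds within a practice, and its odds ratio lies further from 1 whenever practices vary. Their standard errors also rest on different assumptions. The text supports either one as the primary analysis, and the data come as a single extract at the end, so the choice could be made with both results in view.

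The second issue follows if GEE is the intended model. The usual GEE standard error is a sandwich estimate that treats each practice as one independent unit. With few units of very unequal size it tends to be too small, which makes the confidence interval too narrow and the test too liberal. The Discussion's argument about practices acting as their own controls concerns precision and the influence of the ICC. It does not increase the number of independent units in the sandwich.

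**Working it through.** The plan gives no operating characteristic of the primary test beyond the nominal 5%, so there is no figure of its own to reproduce on this point.

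**1. Are the statements compatible?** The Analysis section names a mixed logistic model, then GEE, then gives a reason against random effects, then enters practice as a random effect. The GEE sentence and the random-effect sentence cannot both describe the fitted model. Whichever model a fuller document chose would contradict a sentence here.

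**2. How far apart are the two odds ratios?** The illustration uses 13% and 26%, the pair in the Sample size section's ICC 0.1 example.

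- Marginal odds ratio: (0.26/0.74)/(0.13/0.87) = 0.3514/0.1494 = 2.35; its logarithm is 0.855.
- Between-practice variance on the logit scale, taken as ICC/(p(1−p)) at p = 0.13: 0.05/0.1131 = 0.442 and 0.10/0.1131 = 0.884.
- Standard approximation: practice-specific log odds ratio = marginal log odds ratio × √(1 + 0.346σ²).
- ICC 0.05: 0.855 × √1.153 = 0.918, an odds ratio of about 2.50.
- ICC 0.1: 0.855 × √1.306 = 0.977, an odds ratio of about 2.66.

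**3. What does GEE inference do with 26 practices?**

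- *Inputs from the article:* 26 practices, mean size 240, CV 0.74, 13% treated without the intervention, ICCs of 0.01, 0.05 and 0.1.
- *Assumed, because the article does not fix them:* 6, 13 or 26 steps; cluster autocorrelation 1.0 or 0.8; gamma-distributed practice sizes; outcome as a new start per step or as the proportion on treatment at each step.
- *Model:* logistic GEE with one effect per period plus exposure, on stepped wedge data with no intervention effect. There were 2,000 trials per scenario, so the Monte Carlo standard error is √(0.05 × 0.95/2000) = 0.5 points at 5% and √(0.12 × 0.88/2000) = 0.7 points at 12%.

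| Standard error and reference | Two-sided type I error, nominal 5% |
|---|---|
| Uncorrected sandwich, z, independence | 9.6% to 12.2% |
| Uncorrected sandwich, z, exchangeable | 7.8% to 10.4% |
| Uncorrected sandwich, t on 24 df | 6.1% to 10.8% |
| Mancl-DeRouen, t on 24 df | 3.5% to 6.1% |
| Model-based, exchangeable and correct | 3.8% to 6.0% |
| Model-based, exchangeable, autocorrelation 0.8 | 8.2% to 38% |
| Model-based, independence | 29% to 89% |

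The uncorrected sandwich standard error was 0.80 to 0.92 of the true standard deviation. Under a normal approximation, that shortfall alone gives 2(1 − Φ(1.96 × 0.92)) = 7.1% to 2(1 − Φ(1.96 × 0.80)) = 11.7%, close to the simulated range.

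A separately programmed simulation used practice size as a covariate, ICC 0.05 and 27 three-week time points. It gave 8.3% (exchangeable, 1,500 runs; SE ratio 0.094/0.103 = 0.91) and 12.2% (independence, 1,000 runs; 0.226/0.275 = 0.82).

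**4. Is the number of step effects responsible?** With the uncorrected sandwich and z, the error was 8.4% to 12.2% with 6 steps, 7.9% to 11.3% with 13, and 7.8% to 12.1% with 26. It does not grow with the number of time effects. With 26 single-practice steps, 27 period effects plus exposure make 28 parameters against 26 practices, so the full sandwich matrix cannot have full rank. But inflation of the same size appears with 6 steps, where there are far fewer parameters than practices.

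**5. Solihull.** With 6 practices and 6 assumed steps, the uncorrected sandwich with z gave 24% to 28%. The article expects no adequate power there, so this is secondary.

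**The case against.** The strongest reply is that the intention is clear. The article says how the models will be fitted and why random effects are avoided, so the later phrase may be loose wording for clustering. Both models share the same null hypothesis, and 2.35 against 2.50 or 2.66 is a modest gap. This explains how the text may have arisen, and it supports choosing GEE in the correction. It does not remove the contradiction, since mixed-model wording appears twice and the reported estimate and its interval depend on the choice.

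The reply on standard errors is stronger. A reader might infer that the primary test as planned exceeds 5%. The documents do not support that. They do not say that the errors are robust, uncorrected or referred to a normal distribution, and such detail is commonly left to an analysis plan that is not shown here. Model-based errors with a correctly specified exchangeable correlation stayed near 5%. They are not a safe default, though, because they reached 8% to 38% when the correlation decayed over time.

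A reader might also blame one fixed effect per step, or count 36 parameters (27 time points, exposure, practice size and seven patient covariates) against 26 practices. That does not hold either. The number of steps is not stated, and patients on the diabetic register are excluded, so diabetic status should vary little at entry. The inflation is also about the same with 6, 13 or 26 steps. One set of 400 runs with roughly quarterly time effects gave about 6%, but its 95% Monte Carlo interval is 6% ± 1.96 × √(0.06 × 0.94/400), or about 3.7% to 8.3%. That is too imprecise to justify coarser time effects.

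**Conclusion.** The contradiction in the primary model is established from the text alone and needs no assumption. It affects the one test to which the 5% level applies. In the example used here it moves the odds ratio from 2.35 to about 2.50 or 2.66, and it changes the standard error.

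The inference point is conditional. If the model is GEE with an uncorrected sandwich and a z test, the Sandwell analysis would run at about 8% to 12%, so a nominal 95% interval would cover about 88% to 92% of the time. This held in every scenario tried, across the assumed steps, ICCs and autocorrelations. The cause is the small number of practices. The stepped wedge argument in the Discussion does not remove it, because the simulations were themselves of stepped wedge data. With Mancl-DeRouen and t on 24 degrees of freedom the error was 3.5% to 6.1%.

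**What to change.** In the Analysis section:

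- Name one primary model: a marginal logistic GEE clustered by practice, with exchangeable working correlation, fixed time effects and exposure as the intervention effect. Delete the mixed logistic and random-effect wording.
- For the Sandwell primary analysis, specify a small-sample corrected sandwich, such as Mancl-DeRouen or Kauermann-Carroll, with a t reference (26 − 2 = 24 degrees of freedom was used in the check). Only Mancl-DeRouen was simulated here.
- Optionally, add a sensitivity check that permutes practice order within the strata described under Randomisation. It need not supply the primary p-value.

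No change to the form of the time effects is needed on this ground.

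The cost is a few sentences and modest programming. Intervals will be somewhat wider than uncorrected ones. If the correction restores the standard error to its true size, the factor is about 1/0.92 = 1.09 to 1/0.80 = 1.25, and the t critical value (2.06 instead of 1.96) adds about 5%. Nothing changes in the design, the data extraction or the conduct of the trial.

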[35]. In this setting we are limited by the number of GP practices in the two primary care trusts. However, the stepped wedge nature of this design, in which all practices will eventually receive the intervention, but the order in which they do so will be randomised, does provide a more robust design over the conventional cluster randomized trial and so may mitigate some of the potential issues surrounding the inclusion of what might be considered as a small number of clusters. This is because within a stepped wedge design each clusters acts as its own control (during the period in which the cluster is not receiving the intervention) and it has been shown that magnitudes of intra-cluster correlations are less important
[36]. Furthermore, this study is a modification of the common step-wedge design because after completion of case finding the intervention is not maintained in the clusters (rather the nurse who delivers the intervention moves to the next practice). In effect, this probably means a reduced level of power to detect an effect of the intervention due to contamination of patients not exposed but nonetheless contributing to the analysis in later wedges.

Routine data on prescription of antihypertensives and statins is a pragmatic and easily collected outcome. However this leaves the study vulnerable to primary non compliance as not all those who are issued prescriptions take them.

We hope to be able to determine whether case finding is more effective and cost effective in achieving higher rates of uptake of preventative advice and treatment; whether it results in a reduction in outpatient referrals and admissions to hospital for CVD related events; and whether it is acceptable to clinicians and patients.

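### A single exposed/not-exposed term is fitted although the intervention ends with each practice visit; for new treatment starts this biases the estimate as well as costing power, in a direction that depends on the target effect

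*Protocol article*

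**What the plan says.** The Analysis section of the protocol article builds the primary model from practice, calendar time and "an indicator of intervention exposure for each practice at each time point", and later lists "time point as a fixed effect; and exposure or non-exposure as the main intervention effect". On estimation it says: "These models will be fitted using population averaged models using GEE methods in STATA". It describes no term for time since the visit.

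The Discussion says that "after completion of case finding the intervention is not maintained in the clusters", because the nurse goes on to the next practice. It gives the consequence as follows: "this probably means a reduced level of power to detect an effect of the intervention due to contamination of patients not exposed". These patients are described as "nonetheless contributing to the analysis in later wedges".

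The outcome is worded in two ways. Primary outcomes and Follow up and data collection count high-risk patients newly started on treatment, assessed step by step. The Analysis section states the aim as a before-and-after difference in the proportion of eligible patients who are on medication. Data come from a "single data extract at least one year after targeted case-finding has been implemented in the last practice".

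**The concern.** One indicator assumes one constant effect from the day a practice is reached until the end of the data. New starts are unlikely to behave that way. Patients on the list are invited, assessed and referred during the visit, after which the practice presumably drifts back towards its usual start rate. Practices whose visit ended months ago then share a coefficient with practices being visited now.

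With step effects in the model, the coefficient is learned from steps that contain both exposed and unexposed practices. Early in the roll-out all the exposed practices are recent ones. The mix of visit and post-visit effects is therefore set by the design and not by any stated question.

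The trial sets out to quantify the benefit of case finding. A coefficient that is neither the visit-period effect nor the one-year effect cannot be read as either, and calling the problem reduced power does not warn the reader of that.

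**Working it through.** The article gives no figure for the size or direction of this bias, so there is none to reproduce. The check fits the planned term to expected counts.

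**Inputs from the article.** 26 Sandwell practices averaging 240 eligible patients and a usual start proportion of 13% in a year (Sample size & number of practices); roll-out of about 18 months (Intervention); 41% started in the pilot's intervention practices (Pilot study); 19% as a smaller effect, taken from the detectable values in the sample size section.

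**Assumptions.** One practice is reached per equal step: 78 weeks / 26 = 3 weeks. Extra starts are spread evenly over a burst of *b* steps from the practice's start, then the usual rate returns. Patients who start leave the risk set. Working correlation is independence (the article does not state one). The article says that steps differ in length and gives no burst length, so several are tried.

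**Formulas**, for a true 41% and a 9-week burst (*b* = 3):

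- Steps per year: 52/3 = 17.33.
- Usual risk per step: p0 = 1 − 0.87^(1/17.33) = 0.0080, odds 0.00807.
- Risk per burst step p1, from (1 − p1)^b × (1 − p0)^(17.33 − b) = 1 − 0.41. So p1 = 1 − (0.59/0.8912)^(1/3) = 0.128, odds 0.1474. OR during the visit = 0.1474/0.00807 = 18.3.
- Constant OR that would yield 41% at one year: risk per step 1 − 0.59^(1/17.33) = 0.0300, odds 0.0309, OR = 0.0309/0.00807 = 3.8.
- Logistic model with step effects and one exposure indicator, fitted to expected starts in 26 practices × 27 steps: OR 8.36.
- Implied one-year proportion: odds 0.00807 × 8.36 = 0.0675, risk 0.0632, and 1 − (1 − 0.0632)^17.33 = 68%.

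| True at one year | Burst (weeks) | OR during burst | Constant OR matching truth | Fitted OR | Implied at one year |
|---|---|---|---|---|---|
| 41% | 9 | 18.3 | 3.8 | 8.36 | 68% |
| 41% | 18 | 9.4 | 3.8 | 6.62 | 59% |
| 41% | 27 | 6.5 | 3.8 | 5.51 | 53% |
| 41% | 39 | 4.8 | 3.8 | 4.51 | 46% |
| 19% | 9 | 4.0 | 1.52 | 2.05 | 25% |
| 19% | 18 | 2.5 | 1.52 | 1.89 | 23% |
| 19% | 27 | 2.0 | 1.52 | 1.76 | 22% |
| 19% | 39 | 1.7 | 1.52 | 1.62 | 20% |

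In every row the fitted OR lies above the value that matches the one-year truth and below the visit-period OR. Splitting exposure into burst and later recovers the generating values (18.3 and 1.00 in the first row).

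**Average effect over exposed time.** A second check used the weights that the single-indicator model gives to each step since exposure. The effect was set to 1 in one visit step and 0 afterwards, with about a year of follow-up.

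| Steps in roll-out | Fitted, independence | Fitted, exchangeable (ICC 0.05) | True average over exposed steps |
|---|---|---|---|
| 13 | 0.21 | 0.30 | 0.062 |
| 26 | 0.11 | 0.16 | 0.033 |
| 6 (Solihull) | 0.43 | 0.56 | 0.105 |

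The average is overstated about 3.4 to 5.3 fold (1.5 to 2.9 fold without the follow-up year), while the fitted value is only 11% to 56% of the visit-step effect. A constant effect is recovered exactly. An effect that builds up over four steps is understated (0.71 or 0.60 against 0.91, 13 steps).

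**Outcome read as being on treatment.** The true one-year OR is (0.41/0.59)/(0.13/0.87) = 4.65, and the fitted OR is 5.25, 4.32 and 3.02 for bursts of 9, 18 and 39 weeks. For 19% the true OR is 1.57, and the fitted OR is 1.65, 1.53 and 1.35.

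**The case against.** The Discussion openly says that the intervention is not maintained, and its remark is reasonable if the target is active case finding: in the 9-week scenarios the coefficient is diluted from 18.3 to 8.4 and from 4.0 to 2.05. That stands. A reader might infer that the plan simply overstates the effect; the documents do not support this, because they do not say which effect is meant.

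The one-year conversion is this check's, not a planned output. That is true, but the pilot and the sample size section both speak of the proportion started over a year, so it is a natural yardstick.

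The size rests on a short burst. Invitations go out in order of risk, non-attenders get two further contacts, the GP starts treatment, and more than one nurse may work in parallel. With a burst of 39 weeks the excess is about 5 percentage points (46% against 41%), and it vanishes at one year. This stands.

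The indicator might be meant to switch off after the visit. The article does not say so. It compares the control and intervention sections of the wedge, and it speaks of contamination by unexposed patients in later wedges, which fits an indicator that stays on.

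Two further inferences fail. The article does not say that the exposure odds ratio feeds the Markov model. The follow-up year, which has no unexposed practices, leaves the fitted OR unchanged under independence; it matters only under a correlated structure (26 steps, ICC 0.05: 0.21 without it, 0.16 with it).

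Time-since-visit detail could sit in an analysis plan that is not shown. But the article itself fixes the main intervention term and states its consequence, so both can be challenged as written.

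**Conclusion.** The concern holds with its target named. For new starts that cluster around the visit, the single coefficient overstates the one-year and average post-exposure effects and dilutes the visit-period effect. The estimate is biased as well as less precise.

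The excess in the implied one-year proportion falls from 27 to 5 percentage points as the burst lengthens from 9 to 39 weeks if the truth is 41%, and from about 6 points to 1 if it is 19%. These sizes rest on assumed 3-week steps, a constant usual rate, a return to it after the burst, and independence.

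If the outcome is being on treatment, the bias is small for short bursts and turns downward for longer ones. The test of a strict null, no effect at any time since the visit, is unaffected.

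**What to change.** 1. Reconcile the outcome: new starts (Primary outcomes; Follow up and data collection) or being on treatment (Analysis).
2. State the primary estimand, for example the difference in the proportion started within 12 months of the practice's start date.
3. Replace the single indicator by separate visit-period and post-visit terms, defined by time since the practice's start with the boundary fixed in advance, and derive the estimand from them.
4. Amend the Discussion to say that a single-indicator estimate would be biased as well as less powerful.

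The cost is analysis wording, one extra model term and a small loss of precision. No new data are needed: Table 1 already includes prescription dates, and practice start dates are required for any exposure indicator.
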